### **Revision of the study information sheet and consent form**

If, during the course of the study, the principal (or sub-) investigator obtains new information that may affect the participant’s consent, the study information sheet and consent form must be revised accordingly. Such new information may include newly recognized adverse events or the development of alternative treatments for the target disease. If the revisions are deemed to potentially affect the participant’s decision to continue, the revised documents must be submitted to the ethics committee for approval. After obtaining approval, participants must be re-informed, and new written consent must be obtained.

# **Protection of Personal Information**

To ensure the protection of the participants’ personal information, the following measures are observed in the conduct of this study:

1. When handling subject-related data, sufficient attention should be paid to confidentiality.
2. The personal information handled in this study is limited to what is necessary. The subject’s name is replaced with a study-specific identification number to prevent the immediate identification of individuals.
3. Anonymization is conducted promptly before starting the data analysis.
4. The correspondence table (linking subject names and ID numbers) is submitted to the Research Information Management Office prior to the start of data analysis, in accordance with the institutional policy on personal information management and data protection. Until then, it is stored in a locked drawer of a personal desk in the department under the responsibility of the principal investigator.

# **Data Management**

## **Preparation of CRF**

The principal (or sub-) investigator or study collaborators is enter the observation and assessment data into the CRF. The contents of the CRFs must be consistent with source documents. Data is entered and managed using Microsoft Excel.

## **Amendments or Corrections to the CRFs**

If amendments or corrections to the CRFs are necessary, the responsible personnel do so in accordance with the CRF amendment/correction procedures.

## **Attribution of collected data**

All information obtained in this study belongs to the National Cerebral and Cardiovascular Center and may not be accessed without the principal investigator’s permission.

# **Storage of Samples and Data**

## **Method of Storage**

The following procedures are followed for the storage and management of the samples and data:

1. Electronic study data is stored under the responsibility of the principal investigator in accordance with the information security policy of the National Cerebral and Cardiovascular Center, Japan. Specifically, PCs and storage devices in the department are protected as follows.
   1. Installation and regular updating of antivirus software
   2. Access control using IDs and passwords, allowing access only to authorized research personnel
2. Blood samples for testing are stored in a locked freezer in the equipment room in front of Operating Room 10, under the responsibility of the principal investigator, until they are sent to the commissioned laboratory for analysis.

## **Transfer of Samples/Data to External Organizations**

Transfer of samples/data: Not applicable

## **Retention Period of samples and information**

According to the internal regulations of the National Cerebral and Cardiovascular Center regarding research misconduct, data is retained for 10 years following publication. Residual samples are not stored, as none remain. After the retention period, paper records are shredded or dissolved, electronic data is be deleted, and storage media is physically destroyed to ensure complete anonymization.

## **Future Use of Data**

The samples and data collected in this study is used for the purposes of this study. If future use or sharing for other research arises, it is conducted only after the development of a new protocol and approval by the ethics committee and institution.

# **Quality Control & Quality Assurance**

## **Compliance, Deviations, and Amendments**

The principal (or sub-) investigator and study collaborators must comply with the study protocol in conducting this research. No deviations or changes to the protocol are made without prior approval from the ethics committee. All deviations are documented. However, deviations or changes may be permitted if they are deemed medically necessary.

## **Protocol Amendments**

If new information necessitating a protocol amendment arises, the principal investigator revises the protocol and prepare a record of the revisions and their rationale. Ethics committee approval and institutional permission must be obtained before the implementation. If patient enrollment needs to be suspended during the revision process, the principal investigator must notify the study collaborators accordingly.

## **Monitoring**

Monitoring is conducted by a monitor designated by the principal investigator to assess the study’s framework and implementation. The details are described in a separate monitoring procedure.

## **Audit**

No audit is conducted, as the study is funded solely by the internal research and development funds of the National Cerebral and Cardiovascular Center.

# **Termination or Discontinuation of the Study**

## **Study Termination**

When all analyses and manuscript submissions are completed, the principal investigator notifies the study collaborators of the study’s completion and performs all related closing procedures, including reporting to the head of the institution.

## **Discontinuation or Suspension of the Study**

### **Criteria for Discontinuation or Suspension**

The principal investigator may discontinue or suspend the study if any of the following criteria are met. Notification of discontinuation must be submitted to the ethics committee within 10 days of the decision.

1. Occurrence of serious adverse events or other safety concerns making continuation of the study difficult
2. New information from publications or academic meetings indicates that the study is no longer feasible or meaningful
3. Serious noncompliance with ethical guidelines or related regulations makes continuation difficult
4. Significant delays in enrollment prevent successful completion of the study
5. Any other reason the principal investigator deems discontinuation necessary

### **Procedures for Discontinuation or Suspension**

If the principal investigator determines that the study should be discontinued or suspended based on the above criteria, the following procedures are followed.

1. The principal investigator promptly informs all personnel involved in the decision and the reasons for discontinuation or suspension.
2. The principal investigator promptly notifies affected participants and take appropriate action. In addition, the principal investigator reports the decision to the head of the institution and related departments and follow the prescribed institutional procedures.

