## **Discontinuation Criteria and Procedures for Study Participation**

### **Discontinuation Criteria**

If, for any of the following reasons, the subject is unable to complete the study or must discontinue the administration of the study formulation, the principal investigator (or co-investigator) terminates the subject's participation in the study.

1. The participant requests to withdraw from the study
2. Surgery is cancelled after consent has been obtained
3. For safety reasons, the principal investigator deems it necessary to discontinue participation
4. The study itself is terminated
5. Other reasons determined by the principal or sub-investigator

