## **When the study is stopped early (date of decision to discontinue+3)**

The following observations and tests are performed within three days of study discontinuation.

| 1) Study Treatment Information | |
| --- | --- |
| Discontinuation/interruption of treatment | Presence or absence; if applicable, record the date of discontinuation/interruption, reason, and subsequent management. |
| 2) Clinical and Laboratory Data ^*4^ | |
| Laboratory tests | White blood cell count, hemoglobin, platelet count, total protein, albumin, total bilirubin, direct bilirubin, AST, ALT, creatinine, LDH, CK, CK-MB, sodium, potassium, chloride, calcium, CRP, PT-INR, APTT, fibrinogen |
| 3) Adverse Event Information | |
| AEs | Date of onset, event name, known or unknown, seriousness, severity, causal relationship, treatment, outcome, date of outcome confirmation, readmission status (presence or absence), date of readmission, date of discharge, and other relevant details |
| 4) Outcome Information | |
| Survival status | Outcome: alive, deceased, or lost to follow-up  Date of last confirmed survival or date of death; in case of death: cause of death  If lost to follow-up: reason for loss to follow-up |
| Study withdrawal | If applicable, record the date of withdrawal and the reason |

*4 If test results from other visits or routine clinical care are available within one day prior to the date of study discontinuation, those results are used be used.**Observation and Inspection Schedule**

| Survey Period  Survey Items | Test Period | | | | Early discontinuation |
| --- | --- | --- | --- | --- | --- |
|  | Visit 1 | Visit 2 | Visit 3 | Visit 4 |  |
|  | **Consent, eligibility check, provisional registration** | **Final registration, allocation (prior to study treatment initiation)** | **During study treatment** | **End of Exam** |  |
| Stipulated days | -30 days~ | 0 days | 0 days | 30 days | ― |
| Tolerance | ― | ― | +3 days | ± 5 | +3 days |
| **Informmed consent** | ◎ |  |  |  |  |
| **Basic subject information** | ○ |  |  |  |  |
| **Target disease information** | ○ |  |  |  |  |
| **Study treatment information** |  |  | ○ | ○ | ○ |
| **Oral medication information** | ○ | ○ |  |  |  |
| **Physical findings** | ○^※1^ | ○^※2^ | ○ |  |  |
| **Vital signs** |  |  | ○ |  |  |
| **Laboratory tests (complete blood count, biochemistry, blood type-related, coagulation, viscoelastic testing)** | ○^※1^ | ○^※2^ | ○ | ○^※3^ | ○^※4^ |
| **Blood gas analysis** |  |  | ○ |  |  |

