## **Reporting of AEs**

### **Reporting Period for AEs**

AEs must be reported from the initiation of study product administration until 30 days thereafter or until the final study visit specified in the protocol, whichever is later. Any SAE for which a causal relationship with the study product cannot be ruled out must be reported **regardless of the reporting period**, as long as it occurs before the end of the study period.

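### A study-level stop appears to end follow-up of treated patients at about three days, which conflicts with the 30-day follow-up and AE reporting rules

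*Protocol*

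**What the plan says.** Five parts of the protocol bear on what happens to treated patients if the study stops.

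- **Grounds for a stop (18.2.1).** The first listed ground is "Occurrence of serious adverse events or other safety concerns making continuation of the study difficult".
- **Procedure after a stop (18.2.2).** Study personnel are told. For participants, "The principal investigator promptly notifies affected participants and take appropriate action". The head of the institution and related departments are informed, and the institution's own procedures apply. Follow-up of patients already treated is not mentioned.
- **Ending participation (7.8.1).** For the listed reasons the investigator "terminates the subject's participation in the study". Item 4 on the list is "The study itself is terminated". Patients already treated are not excepted.
- **Early stop (8.5).** "The following observations and tests are performed within three days of study discontinuation". The schedule shows this as its own early-discontinuation column (+3 days), beside Visit 4 at day 30 ± 5.
- **Safety follow-up.** The study overview gives an observation period of 30 days after treatment. Section 9.4.1 says: "AEs must be reported from the initiation of study product administration until 30 days thereafter or until the final study visit specified in the protocol". The later of these two dates applies. Neither place has an exception for a stopped study.

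**The concern.** The rules for a stop and the rules for follow-up give staff different instructions for the same patient. Sections 7.8.1 and 8.5 read together suggest closing the patient out within three days. Section 9.4.1 and the overview require observation to day 30. Section 18.2.2 is where this should be settled, and it leaves the matter to unspecified action.

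The conflict matters most in a safety stop. The most recently treated patients then have the least follow-up, and they are among those whose course has to be examined. If site staff follow the three-day route, the trial may miss later infections, deaths and AEs that are judged unrelated or have not yet been noticed. It would also have no scheduled entry for outcome items that appear only in the Visit 4 list.

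**Working it through.** The protocol gives no figure on this point, so the check is a comparison of text followed by a rough count of patients affected.

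**1. The path after a study-level stop**

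| Step | Section | Effect on a treated patient |
|---|---|---|
| Study stopped for safety | 18.2.1, item 1 | Stop permitted |
| Participation | 7.8.1, item 4 | Investigator ends it |
| Next scheduled assessment | 8.5 | Within 3 days of the stop |
| Further follow-up | 18.2.2 | Not addressed |
| AE reporting | 9.4.1 | To day 30 or the final visit, whichever is later |
| Observation period | Study overview | 30 days |

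The first four rows lead to about day 3 after the decision, and the last two lead to day 30. A patient treated d days before the decision has the early-stop assessment by day d + 3, which is 30 − (d + 3) = 27 − d days short of day 30. For a patient treated on the day of the decision (d = 0) the gap is up to 27 days.

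**2. Does another rule close the gap?**

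- Section 7.7.1 keeps data collection going, but only when study treatment is discontinued.
- Section 7.8.2 ends data collection in words only for voluntary withdrawal. It neither bars nor requires later data after a study stop.
- Section 9.2 follows causally related AEs, in principle, until they resolve or stabilise.
- Section 9.4.1 keeps SAEs reportable beyond the period if a causal link cannot be ruled out, "as long as it occurs before the end of the study period".

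Related events are therefore covered. AEs judged unrelated, and events nobody is scheduled to look for after about day 3, depend on which rule staff follow.

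**3. Items scheduled only at Visit 4**

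Under study treatment information, the 8.5 list has only discontinuation or interruption of treatment. The 12-hour chest tube loss, the transfusion volume after ICU admission, ventilation time and length of ICU stay are in the Visit 4 list (8.4). A patient routed to 8.5 has no scheduled entry for them, although the values would normally be in the clinical record.

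**4. How many patients**

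Input from the protocol: 142 final registrations (section 11). The approval date and accrual rate are not given, so even accrual over 12 to 36 months is an assumption.

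Number inside a window of w days at any stop date = w × 142 / (months × 30.4375).

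| Accrual (months) | Patients per day | Inside 30 days | Inside 7 days |
|---|---|---|---|
| 12 | 142/365.25 = 0.389 | 11.7 | 2.7 |
| 18 | 142/547.9 = 0.259 | 7.8 | 1.8 |
| 24 | 142/730.5 = 0.194 | 5.8 | 1.4 |
| 36 | 142/1095.75 = 0.130 | 3.9 | 0.9 |

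The 7-day column is shown because acute kidney injury is assessed to day 7 (section 4.3).

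**The case against.** The strongest reply is that nothing in the protocol cancels Visit 4. Section 8.5 does not call its assessment the last one, and the protocol says expressly that data collection ends only for withdrawal of consent. A reader might infer that later follow-up is forbidden after a stop. The documents do not support that, and the three-day assessment could be read as an additional check. This stands: the cut is the plain reading of 7.8.1 with 8.5, not an express rule. It leaves the conflict with 9.4.1 in place, because no section says which rule governs.

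The link through 7.8.1 can also be questioned. Its opening condition concerns subjects who cannot complete the study or must stop the study product, and administration is already over once the patient leaves the operating room. Section 18.1 uses termination for normal completion, while 18.2 speaks of discontinuation. The items in 8.5 would also suit one patient's early exit. These points show loose drafting. Still, the 8.5 heading refers to the study being stopped early, and item 4 of 7.8.1 makes a study stop a reason for individual exit, so either reading leads to the same column.

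Third, safety cover is better than it may look. Related AEs and SAEs remain covered, and 9.3.3 sets a low threshold for not ruling out causality. This stands and narrows the loss to the categories named above. That cover still depends on the event being noticed.

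Two further inferences should be resisted. One is that day-30 laboratory results would be lost: Visit 4 laboratory data are those of the day after surgery, so none would be. The other is that event rates would be understated: that depends on how the analysis treats incomplete follow-up, and the protocol does not show it.

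**Conclusion.** The point holds as a conflict between stated rules. After a study-level stop, 7.8.1 item 4 and 8.5 point to exit with one assessment within three days, while the overview and 9.4.1 require 30 days without exception. Section 18.2.2 does not reconcile them.

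Its reach is small and conditional. It arises only if the study is stopped early. Assuming even accrual of 142 patients over 12 to 36 months, about 12 to 4 treated patients would be inside their 30-day window, and about 3 to 1 inside the 7-day kidney injury window. The share of all exposed patients cannot be given, because it depends on when a stop occurs. The exposure is to missed unrelated AEs, undetected infections and deaths, and unscheduled Visit 4 items. It is worth correcting because the remedy is cheap and the patients concerned are the most recently exposed.

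**What to change.** Reconcile 7.8.1, 8.5, 9.4.1 and 18.2.2.

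- In 18.2.2, state that after a study-level stop or suspension no new patient is registered, and that participants already randomised who have not withdrawn consent are followed from routine records to Visit 4. That follow-up covers AEs and SAEs, the three safety outcomes, survival and the Visit 4 data items.
- In 8.5, state that after a study-level stop the three-day assessment is additional to Visit 4 and does not replace it for these participants.
- In 7.8.1, word item 4 to agree with this, using the same term for an early stop as 18.2.

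The change affects only what is observed and recorded. It costs a wording amendment, about one month longer to close a stopped study, and chart follow-up of roughly 4 to 12 patients (on the accrual assumption above) using items already in the schedule.

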# **Funding and Conflict of Interest**

## **Funding**

This study is self-funded by the National Cerebral and Cardiovascular Center. The funding source is not be involved in the design, management, analysis, or interpretation of this study.

## **Conflict of Interest**

This study is funded by the 2023 fiscal year budget for cardiovascular disease research and development. No commercial entity is involved, and there is no conflict of interest to disclose.
Any potential conflict of interest must be reported to the Conflict of Interest Committee for Medical Research and approved by it. This study ensures that no disadvantage arises for the participants as a result of any conflict of interest.

# **Compensation for Study-related Injury**

If a study-related injury occurs, the institution provides appropriate and optimal care to the participant. As this study involves the use of blood products that are already in routine clinical use, any adverse reactions are treated as part of standard care, and no additional compensation (e.g., reimbursement of out-of-pocket expenses, condolence payments, or disability compensation) is provided. In applicable cases, compensation may be sought through the pharmaceutical adverse reaction relief system.

No clinical trial insurance is purchased for this study.

# **Post-study Medical Care for Participants**

After study completion, the participants continue to receive treatment under standard insurance-based care.

# **Handling of Study Results and Health Information**

Participants are informed that this study is not expected to yield new, individual health-related results.

# **Publication and Ownership of Study Results**

## **Study Registration**

Before the enrollment of the first participant begins, the study overview is registered in the Japan Registry of Clinical Trials, and the progress and results are updated accordingly.

## **Publication of Study Results**

After the study is completed, the results are published in academic journals or presented at conferences by the designated authors. Prior to publication, the authors consult with the principal investigator and other stakeholders and obtain approval. The approval number for the study will be included in all publications.

## **Ownership of Study Data and Results**

Intellectual property arising from this study, in principle, belongs to the institution, in accordance with internal regulations on employee inventions. The ownership does not extend to the participants or their families.

# **Study Implementation Structure**

See the attached document: Study Implementation Structure.

# **Oversight of Contracted Organizationss**

Outsourcing: Yes

1. Contract organization: SRL
2. Provided item: Measurement of heparin concentration
3. Details of contracted service: Measurement of heparin concentration in salvaged RBC
4. Oversight method: Compliance with the contract is checked as required. Any identified issues are addressed accordingly.

